### Data collection, data sources, and monitoring

Unidentified patient data are routinely collected for the IMPACTO-MR platform by all ICUs and include data on demographics, baseline characteristics, admission diagnosis, severity score (Simplified Acute Physiology Score [SAPS] 3), ICU and hospital length of stay, and mortality. Additional data on HCAIs are collected through a digital online case report form developed by the HCor data management team using REDCap^®^.^(
32
,
33
)^ Additionally, data on antibiotic use during the ICU stay and the results of microbiological cultures collected during the ICU stay are collected from all participating centers using prescription, pharmacy, and microbiology laboratory records.

Access to all data platforms is password protected and supported by the HCor data management team. Data monitoring is performed by the HCor data management team. All data on HCAIs will be monitored, either
*in loco*
or online.

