### Sample size

Initially, the study was expected to include between 30 and 50 ICUs of the IMPACTO-MR platform, with an expected sample size of 30,000 patients (
Figure 1S - Supplementary Material
). However, owing to feasibility issues and restrictions on the study’s budget provided by the Brazilian Ministry of Health after December 31, 2023, the sample size was recalculated considering possible variations in the number of clusters, cluster size, and data from the IMPACTO-MR database to estimate the baseline rate of HCAIs. Therefore, by including 12,600 patients (21 clusters with a mean of 600 patients each) with a baseline rate of 6 HCAIs per 1,000 patient-days and a between-cluster variance of 0.6, our study will be able to detect a 9% (relative risk of 0.91) reduction in the incidence of HCAIs, with 80% power and an alpha of 5% (
Figure 2S - Supplementary Material
). Details are provided in the
Supplementary Material
.

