### Statistical analysis

The main analysis will follow the intention-to-treat framework with patient-level data. Each patient will be analyzed according to the group (CHG or soap and water bath) assigned to the ICU at admission, irrespective of the length of stay and the number of days the patient received each intervention. Patients whose stay crosses into another treatment period will be analyzed according to their initial assignment, and patients admitted during the washout period will not be included in the intention-to-treat analysis. We will perform a sensitivity analysis including only patients admitted and discharged during the same intervention period.

The primary outcome of HCAI incidence per 1,000 patient-days will be analyzed using a Poisson generalized mixed linear model with allocation group, study period, and the interaction of allocation group and study period as fixed effects and center as a random effect. Other possible distributions and models might be considered according to the variable’s behavior. We will use the same model to evaluate the incidence per 1000 patient-days of each specific HCAI (CLABSI, VAP, and CAUTI), rates of positive microbiological cultures for multidrug-resistant pathogens, and antibiotic use. Mortality will be assessed using survival and logistic regression models, taking the center, allocation group, and study period as random effects and the interaction of the allocation group and study period as a fixed effect. Generalized mixed linear models with appropriate distributions will be utilized for other outcomes. Preplanned subgroup analyses will be conducted according to the following characteristics: surgical
*versus*
nonsurgical admission, SAPS 3 score ≤ 40
*versus*
> 40, public
*versus*
private ICU, and ICU length of stay ≤ 7
*versus*
> 7 days.

No adjustments for multiplicity will be performed, and a 2-sided p value of less than 0.05 will be considered statistically significant. All the statistical analyses will be performed using R software (R Foundation for Statistical Computing, Vienna, Austria; https://www.R-project.org/).^(
30
)^

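### Severity as an effect modifier is described only as a split of SAPS 3 at 40; if modification is roughly linear in a near-normal score, this loses at least about 36% of the interaction information, so the collected score should carry the main severity analysis

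*Protocol article*

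**What the plan says.** The Statistical analysis section announces the subgroups with "Preplanned subgroup analyses will be conducted according to the following characteristics". Four follow: type of admission, severity, public or private ICU, and length of ICU stay. Severity enters as "SAPS 3 score ≤ 40" versus > 40. The article does not explain why 40 was chosen, does not name an interaction test for any subgroup, and describes no analysis using SAPS 3 as a continuous quantity.

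The material for one is available. The section on data collection lists the "severity score (Simplified Acute Physiology Score [SAPS] 3") among the items that all ICUs routinely supply to the platform. The Statistical analysis section also says "The main analysis will follow the intention-to-treat framework with patient-level data", and that the primary outcome "will be analyzed using a Poisson generalized mixed linear model with allocation group, study period, and the interaction of allocation group and study period". Those terms are fixed, and the ICU is random. A patient-level term can be added to such a model.

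On error control the same section states: "No adjustments for multiplicity will be performed, and a 2-sided p value of less than 0.05 will be considered statistically significant".

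**The concern.** A single cut treats patients scoring 41 and 90 as alike and patients scoring 40 and 41 as different. It describes the truth well only if the effect of chlorhexidine bathing changes abruptly at 40 and is flat on both sides. If the effect changes gradually with severity, the split discards the variation within each group. The comparison between the groups is then less precise than the data allow.

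Two errors become more likely: a real gradient with severity is missed, or a noisy estimate in the smaller group is over-read. The second matters somewhat more because there is no multiplicity adjustment and p < 0.05 is the stated threshold. What is at stake is the reading of one secondary subgroup analysis.

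**Working it through.** **No figure to reproduce.** The article gives no SAPS 3 mean or SD, no share of patients at or below 40, and no subgroup power. The power statement in the Sample size section concerns the primary comparison and is not used as evidence here.

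**1. Information kept by a split.** Assume a normal score and an interaction linear in the score. The information kept by a two-group split, relative to the continuous score, is the squared correlation between the score and the group indicator:

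retained = φ(z)² / [p(1 − p)], with z = (40 − mean)/SD and p = Φ(z), the share at or below 40.

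The best case is an even split: z = 0, φ(0)² = 0.159, and 0.159/0.25 = 0.637. So at least 1 − 0.637 = 36% is lost under this model, wherever the cut falls.

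**2. A cut at 40, SD 15 (mean and SD are assumptions).** The last column is the power of the split where the continuous test has 80%: Φ(2.80 × √retained − 1.96).

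| Assumed mean | z | p | Retained | Loss | Power of split |
|---|---|---|---|---|---|
| 40 | 0 | 0.50 | 0.637 | 36% | 61% |
| 45 | −0.33 | 0.37 | 0.611 | 39% | 59% |
| 50 | −0.67 | 0.25 | 0.541 | 46% | 54% |
| 55 | −1.00 | 0.16 | 0.439 | 56% | 46% |

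**3. Sensitivity to the assumed distribution.** With SD from 12 to 18, the loss is 38–40% at mean 45, 43–51% at mean 50 and 51–65% at mean 55. Simulation over means of 40 to 60 and SDs of 12 to 18 gave 36% to 77% for normal scores and 37% to 86% for gamma scores. Weighting by events instead of patients, with an assumed rate ratio of 1.3 per 10 points, gave 38% to 91% across both shapes. The floor near 36% is stable. The upper end depends entirely on where 40 lies in the distribution.

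**4. Sensitivity to the shape of modification.** If the effect truly steps at 40, the split is the correct form and loses nothing. The linear term then loses information instead.

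**5. Scale on the rate-ratio axis (illustration).** The Sample size section gives "by including 12,600 patients (21 clusters with a mean of 600 patients each"). Its rate assumption is worded "with a baseline rate of 6 HCAIs per 1,000 patient-days and a between-cluster variance of 0.6", and its target relative risk is 0.91. Length of stay is not stated; assume 7 days.

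- Events: 12,600 × 7 × 0.006 × (1 + 0.91)/2 ≈ 505, of which about 265 under soap and water and 241 under chlorhexidine.
- Assume events divide 25/75 across the cut, as patients would at mean 50 and SD 15: 66 and 198 under soap and water, 60 and 181 under chlorhexidine.
- Split: SE = √(1/66 + 1/198 + 1/60 + 1/181) = 0.206. Detectable ratio of rate ratios at 80% power: exp(2.80 × 0.206) = 1.78.
- Equivalent contrast from the continuous score: SE = 0.206 × √0.541 = 0.151, and exp(2.80 × 0.151) = 1.53.
- Other stays scale the SE by √(7/stay). At 5 days the pair is about 1.98 and 1.65; at 10 days about 1.62 and 1.43.

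Clustering and overdispersion are ignored in both forms, so all these ratios are optimistic.

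**The case against.** **This is convention, not error.** A prespecified two-level severity subgroup is common and contradicts nothing in the article. The modelling of heterogeneity is often left to an analysis plan. That is fair as to weight, and it is why the point is minor. But the article does fix the cut at 40, and it can be judged as a choice.

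**A reader might infer that severity will be tested only through this split.** The article does not support that. It announces subgroup analyses without naming an interaction test, and the Supplementary Material and any analysis plan are not shown. What can be said is that no other severity analysis is described in the article.

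**A reader might infer a known loss, such as 40–55%, or that 40 lies well off the centre of the score.** Neither can be taken from the documents. A loss of 40–55% corresponds to about 17% to 34% of patients on the smaller side of the cut, and no such share is given. With a mean of 40 or 45 and SD 15, the loss is 36% or 39%.

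**The loss depends on linearity.** This stands. If modification is a threshold near 40, the split is the better analysis. The documents do not indicate which shape holds, which is why the two-group estimates should be kept and a spline added.

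**The practical gain is small.** This stands in part. The 25/75 division of events assumes equal stay and infection rate across severity, which is doubtful. Even a ratio of 1.53 around an average of 0.91 implies rate ratios of about 0.66 and 1.01, or 0.82 and 1.25, in the two groups. Either analysis would detect only strong modification. The continuous form is still the more informative one under gradual modification, and it uses data already held.

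**Conclusion.** The point holds as a minor improvement. The only analysis of effect modification by severity that the article describes is a split at 40, given without a reason, although the score is collected and the analysis is at patient level. Under a roughly normal score and roughly linear modification, the split loses at least about 36% of the interaction information. Anything more specific is an assumption: with SD 15, about 36%, 39%, 46% and 56% for means of 40, 45, 50 and 55. Under a true step at 40 the split loses nothing.

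A reader might also infer that the trial's main result is weakened. It is not: the primary estimate does not depend on how SAPS 3 is used in a subgroup analysis.

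**What to change.** Add a sentence to the Statistical analysis section, for example:

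> Effect modification by severity will be assessed mainly through an allocation-by-SAPS 3 interaction using the continuous score (linear, with a restricted cubic spline as a check); estimates for SAPS 3 ≤ 40 and > 40 will be shown for display.

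The model needs SAPS 3 as a main effect alongside the interaction. If the spline shows clear departure from linearity, the spline-based description should be reported with the linear result.

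The cost is one sentence and a few model terms, with no new data. The downside is the linearity assumption, which the spline checks. The Perspective section says that inclusion had ended and the database was not yet closed at the time of writing. The change should therefore be dated and made before the comparative analysis; if that analysis has already been run, the continuous interaction should be reported as post hoc.

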## INTRODUCTION

Health care-associated infections (HCAIs) are common preventable illnesses in hospitalized critically ill patients^(
1
)^ and are associated with increased health care costs, length of stay, and mortality.^(
2
-
5
)^ Critically ill patients are at increased risk for HCAIs due to a myriad of factors, such as the use of invasive devices (endotracheal tubes, central lines, and urinary catheters) and their underlying critical illness. Practices such as care, device insertion bundles, and hand hygiene are the cornerstones of infection prevention^(
6
-
9
)^ and a major focus of infection and prevention control services, with several clinical trials evaluating infection prevention strategies in the critical care setting.^(
10
-
15
)^

Chlorhexidine digluconate (CHG) is a water-soluble, low-foaming, topical antiseptic agent included on the list of essential medicines of the World Health Organization;^(
16
)^ CHG exhibits activity against gram-positive and gram-negative bacteria, yeasts, and lipophilic viruses with a possible benefit of residual antibacterial activity.^(
17
)^ Chlorhexidine digluconate has been used in impregnated vascular catheter dressings, skin preparation for invasive procedures, preoperative bathing, and oral decontamination.^(
18
-
20
)^

The use of daily bathing with CHG to reduce HCAIs in critically ill patients has been evaluated in several studies, with mixed results indicating that it decreases the risk of some infections (central line-associated bloodstream infection [CLABSI] and bacteremia) while increasing the risk of others (ventilator-associated pneumonia [VAP]).^(
14
,
15
,
21
,
22
)^ The role of CHG bathing in reducing HCAIs has not been properly evaluated in low- and middle-income countries (LMICs), where the incidence and burden of HCAIs are greater.^(
1
,
23
,
24
)^ A cluster randomized design is desirable when studying interventions to reduce HCAIs given the possible benefit of the spillover effect and the reduction of contamination between the treatment and control groups.^(
25
,
26
)^

The Daily Chlorhexidine Bath for Health Care Associated Infection Prevention (CLEAN-IT) trial is a cluster randomized crossover trial to evaluate the use of daily chlorhexidine bathing in critically ill patients in reducing device-associated HCAIs (CLABSI, catheter-associated urinary tract infection [CAUTI], and VAP) compared with soap and water bathing.

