### Study outcomes

The primary outcome is the incidence of device-associated HCAIs (CLABSI, VAP, and CAUTI) during the ICU stay within each intervention period. The diagnosis of device-associated HCAIs is made according to the
*Agência Nacional de Vigilância Sanitária*
(ANVISA) definitions.^(
31
)^

The secondary outcomes are the incidence of each specific HCAI (CLABSI, VAP, and CAUTI) within each intervention period, rates of positive microbiological cultures for multidrug-resistant (MDR) pathogens within each intervention period, antibiotic use (measured by days of therapy [DOT] or defined daily dose [DDD]) within each intervention period, ICU and hospital length of stay up to 90 days, and ICU and hospital mortality up to 90 days.

Detailed information on the outcomes and study definitions is available in the
Supplementary Material
.

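### One preplanned subgroup splits patients by realised ICU length of stay, a post-allocation outcome linked to infection, so its strata are not randomised comparisons

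*Protocol article*

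**What the plan says.** The Statistical analysis section introduces the subgroups with "Preplanned subgroup analyses will be conducted according to the following characteristics: surgical" and closes the list with "private ICU, and ICU length of stay ≤ 7" versus more than 7 days. The other three factors are surgical or nonsurgical admission, SAPS 3 score (40 or less versus more), and public or private ICU.

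Four other statements bear on the split:

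- **Allocation** (Statistical analysis): "Each patient will be analyzed according to the group (CHG or soap and water bath) assigned to the ICU at admission". The assignment holds whatever the later stay turns out to be.
- **Secondary outcomes** (Study outcomes): "ICU and hospital length of stay up to 90 days, and ICU and hospital mortality up to 90 days".
- **Primary outcome scale** (Statistical analysis): "The primary outcome of HCAI incidence per 1,000 patient-days", modelled with a Poisson mixed model.
- **Infection and stay** (Introduction): device-associated and other health care-associated infections (HCAIs) "are associated with increased health care costs, length of stay, and mortality".

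The article gives no predicted stay, landmark rule or caveat for this subgroup. It applies no multiplicity adjustment and uses a two-sided 5% threshold.

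**The concern.** Three of the four subgroup factors are properties of the admission or of the unit. The fourth is known only once the patient has left the ICU, by which time the primary outcome has or has not occurred. It can be related to that outcome in three ways:

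1. Infected patients tend to stay longer, so infection itself moves patients into the long-stay stratum.
2. If bathing prevents infection or changes stay by another route, the two arms contribute different kinds of patient to the same stratum.
3. Death also ends an ICU stay, so the short stratum mixes early deaths with early recoveries.

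Stay also forms the denominator of the rate, so the split acts on both parts of the quantity being compared. What is at stake is the interpretation of one subgroup. Stratum rates and event counts would partly reflect the split, and a difference between strata could not be attributed to chlorhexidine working differently in short and long stayers.

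**Working it through.** The article states no figure for this subgroup, so there is nothing to reproduce. The structural point follows from the text: allocation is at admission, stay is realised later, and stay is a listed outcome. The calculations below only gauge its size.

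**Inputs from the article:** 12,600 patients, 6 HCAIs per 1,000 patient-days, target relative risk 0.91 (all from Sample size), cut at 7 days (Statistical analysis).

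**Assumed, not in the article:** the distribution of stay, the day from which infection can occur, and the days added by infection.

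**Step 1. Expected events.** With an assumed mean stay of 7 days, 12,600 × 7 × 6/1,000 = 529 HCAIs. The simulation in step 2 gives about 500.

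**Step 2. Where the events fall.** Infection-free stay is lognormal with mean 7 days and coefficient of variation 1; the infection hazard is 0.0083 per day from day 2. Then σ² = ln(1 + 1²) = 0.693, σ = 0.833, μ = ln 7 − 0.693/2 = 1.599. The share with an infection-free stay of 7 days or less is Φ((ln 7 − 1.599)/0.833) = Φ(0.416) = 66%. Once infection adds days, about 65% remain in the short stratum.

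| Days added by infection | Share of HCAIs in short stratum | Of about 500 |
|---|---|---|
| none | about 23% | about 115 |
| exactly 4 | 1.4% | about 7 |
| mean 4, exponential | about 8% | about 40 |
| exactly 7 | 0% | 0 |
| mean 7, exponential | about 5% | about 25 |

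The zero for exactly 7 days is forced by the assumption. An infected patient counts as a short stayer only if infection-free stay plus 7 is at most 7, which is impossible when infection starts after day 2. If 30% of infected patients died soon after infection (a further assumption), the short-stratum share would rise to about 14-17%.

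**Step 3. Stratum rates when every patient has the same hazard.** This uses a different set of assumptions: infection-free stay lognormal with median 4 days and log-SD 0.9, capped at 90 days; constant hazard of 6 per 1,000 patient-days; exponential added days.

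| Mean days added | Rate, stay ≤ 7 | Rate, stay > 7 |
|---|---|---|
| 0 | 5.9 | 5.7 |
| 5 | 2.5 | 7.5 |
| 10 | 1.5 | 7.7 |

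One common hazard appears as a three- to five-fold difference (7.5/2.5 = 3.0; 7.7/1.5 = 5.1) created by the split.

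**Step 4. Effect on the comparison between arms, same model.**

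| Common hazard ratio | Mean days added | Rate ratio ≤ 7 | Rate ratio > 7 | In short stratum, control vs CHG |
|---|---|---|---|---|
| 0.91 | 5 | 0.91 | 0.92 | 72.5% vs 72.6% |
| 0.91 | 10 | 0.91 | 0.92 | 72.2% vs 72.3% |
| 0.50 | 10 | 0.50 | 0.54 | 72.2% vs 72.8% |

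If bathing works only through infection, the relative comparison is almost undisturbed at the planned effect.

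**Step 5. If bathing changes stay itself.** Suppose bathing has no effect on the infection hazard, sicker patients stay longer and are at higher risk, and infection adds a mean of 5 days. If bathing shortened stay by 5%, the rate ratios were 1.06 (short) and 1.03 (long); at 10% they were 1.07 and 1.06. Both exceed 1 because patients of intermediate severity move from the long to the short stratum and raise the rate in each. Against the planned effect on the log scale, ln 1.03 / |ln 0.91| = 0.030/0.094 = 0.31 and ln 1.07 / |ln 0.91| = 0.068/0.094 = 0.72. The spurious effect is thus about a third to nearly three quarters of the one the trial seeks.

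**The case against.** The best defence accepts that the variable is post-allocation and disputes the harm. At relative risk 0.91 membership shifts by about 0.1 percentage point, and both stratum rate ratios stay near the common value. Only one secondary look is affected. All of this stands, and it limits the point.

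It also rules out several stronger readings that a reader might draw:

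- **Any apparent benefit confined to long stayers would be an artefact.** The calculations do not show this. With a common hazard ratio the split does not produce a long-stay-only effect; at hazard ratio 0.50 with 10 added days it leans slightly the other way (0.50 short, 0.54 long). The supported statement is that such a finding could not be interpreted.
- **The short stratum is nearly empty by construction, with perhaps 0-10 events.** That holds only when every infected patient gains the same fixed number of days. With variable prolongation, or early deaths after infection, the count is several times larger. Even with no prolongation the short stratum has few events for its size, because short stays contribute less time at risk.
- **Infection lengthens stay, on the protocol's own word.** The Introduction says only that the two are associated. The defect does not need causation, since stay is a post-allocation outcome either way.

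A further fair objection is that splitting follow-up time at day 7 does not restore randomisation either. Patients still in the ICU on day 8 have been selected by discharge, death and infection. This is correct and must be stated with any such analysis.

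**Conclusion.** The point holds in a limited form. Realised ICU stay is not a valid baseline subgroup factor, its strata are not randomised comparisons, and a difference between them could not be taken as effect modification. That conclusion rests on the article's text alone.

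The size rests on assumptions about stay and prolongation that the article does not give. With mean stay 7 days and risk from day 2, about 65% of patients but roughly 1-8% of HCAIs fall in the short stratum if infection adds a mean of 4 days, 0-5% if it adds 7, and about 23% if it adds none. Rates and event counts by stratum can therefore be heavily shaped by the split. Rate ratios are little distorted at 0.91 when bathing acts only through infection, and more so if it alters stay. The primary analysis and the other three subgroups are untouched. This should be corrected, but it does not threaten the trial's main result.

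**What to change.** Remove ICU length of stay from the preplanned subgroup list and keep surgical admission, SAPS 3 score and public or private ICU.

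If the team wants to know whether the effect depends on duration of exposure, split follow-up time instead of patients. Count HCAIs and patient-days in ICU days 1-7 and from day 8 onward for everyone, and add an allocation-by-window term to the primary model. Infections are then counted when they occur, and no patient is classified by a later stay. Label the analysis exploratory and state that the later window still conditions on remaining in the ICU.

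The cost is a change of wording and the loss, or downgrading to exploratory, of one subgroup result. The time split needs admission, discharge and infection dates. The article does not list infection dates explicitly, but attributing infections to intervention periods already requires them. The Perspective section places analysis after database closure, so when the article was written the change could still be made and documented beforehand.
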